## Abstract

**Background:**

Ban-Lan-Gen (BLG) is a traditional Chinese herbal medicine. It has been used for the prevention and treatment of virus-related respiratory diseases such as influenza virus infection. BLG contains some antiviral compounds, but few evidence-based clinical studies have been conducted to assess its efficacy against influenza. We assessed the effects of BLG (including efficacy and safety) on the treatment of seasonal influenza in an evidence-based clinical trial.

**Methods/Design:**

We conducted a randomized, double-blinded, oseltamivir- and placebo-controlled, parallel-design clinical trial. A total of 177 subjects are going to be recruited after satisfying the criteria: (i) 18 to 65 years of age; (ii) illness onset within 36 h; (3) axillary temperature ≥38.0°C; and (iv) positive influenza (type A/B) virus test. Subjects will be assigned randomly into three groups in equal proportions: oseltamivir treatment, BLG granule treatment, and placebo treatment. Each group receives 5-day treatment and is followed up 1, 3, 5, 7 and 21 days later. Symptoms and patient compliance are recorded, and virus/serum viral antibodies tested. We will use the primary outcome, secondary outcome, and safety indicators to evaluate the efficacy and safety of BLG granules in the treatment of seasonal influenza.

**Discussion:**

We have described the first clinical trial for treatment using a single herb against influenza A and B viruses in China. We will hold a large-scale clinical trial to comprehensively evaluate the effectiveness and safety of BLG against influenza infection based on the results of this pilot study. And this clinical trial will serve as an example for the study of other traditional herbal medicines in evidence-based clinical trials.

**Trial registration:**

This study has been registered at ClinicalTrials.gov: NCT02232945 (3 September 2014).

**Electronic supplementary material:**

The online version of this article (doi:10.1186/s13063-015-0645-x) contains supplementary material, which is available to authorized users.

## Background

### The influenza epidemic

Influenza is an acute respiratory disease caused by highly infectious influenza viruses such as H1N1, H3N2, H5N1, H7N9, and influenza B. It has a strong capability of spreading globally, leading to adverse health effects [1]. Such respiratory diseases are usually caused by type A or type B influenza, and the symptoms include headache, muscle aches, cough, and sudden fever [2]. Infection by the pandemic (H1N1) 2009 virus emerged initially in Mexico in early 2009 and has become a global pandemic [3-5]. Now, influenza A (H1N1, H3N2 and pandemic (H1N1) 2009) and influenza B have induced co-infection worldwide, thereby causing considerable panic among general populations.

### Drug resistance in Western medicine

M2 ion channel blockers (for example, amantadine and rimantadine) and neuraminidase (NA) inhibitors (for example, oseltamivir, zanamivir, and peramivir) are commonly used for the prevention and treatment of influenza [6]. Amantadine and rimantadine, however, have been associated with neurologic toxicities and gastrointestinal side effects [7]. Moreover, overuse of these medicines has been found to result in drug-resistant strains [8]. Up to 2003, M2-resistant variants had even spread to countries where these drugs are used infrequently [9]. Pandemic (H1N1) 2009 has demonstrated resistance to amantadine and rimantadine [10,11]. Our previous study suggested that clinical isolates of H1N1 and H3N2 developed amantadine resistance at 93.1% and 100%, respectively, in Guangzhou, China [12]. NA inhibitors, in comparison with M2 ion channel blockers, are more commonly used but they (i) can also cause respiratory side effects and even death (for example, oseltamivir [13]) owing to intensive use and (ii) have a higher barrier for resistance if overused. A survey from 1999 and 2007 showed a very low level (<1%) of resistance to oseltamivir [10,14], but a survey between 2008 and 2009 reported the resistance to be ≥90% [15-18]. Resistance to zanamivir has been (albeit rarely) reported among immunodeficient patients [19,20]. Whether such antiviral agents can be used to address influenza epidemics is not clear. Furthermore, the true effectiveness of oseltamivir treatment against influenza is controversial [21].

### Traditional Chinese herbal medicine and basic research

Traditional Chinese herbal medicine (TCHM) is richly used in Chinese clinics and widely used to treat and prevent respiratory infection disease. Unlike Western medicine, TCHM has different mechanisms and targets of action and, potentially, could be used to overcome drug resistance and side effects. Therefore, exporting the new antiviral medicine from TCHM will be a new choice. For example, the starting material (shikimic acid) for the synthesis of the oseltamivir can be obtained from *Illicium verum*, which is a type of TCHM (Tamiflu™, Roche, Basel, Switzerland).

Among the many types of TCHMs, Ban-Lan-Gen (BLG) has a thousand-year history of use for the prevention and treatment of respiratory tract infections (particularly respiratory viral diseases). BLG was highlighted as a classic antiviral and anti-influenza agent in the *People’s Republic of China Pharmacopoeia* in 1979 and 2010, respectively. Additionally, BLG was one of the eight major medicines recommended by the Chinese government for the prevention and control of severe acute respiratory syndrome (SARS).

Several clinical studies have evaluated the efficacy of BLG granules on treatment of acute pharyngitis (among which, 50% are caused by viruses), infection of the upper respiratory tract, and influenza H1N1 [22,23]. However, none of those studies were evidence-based clinical trials.

The *Isatis indigotica* root (*IIR*) is the single largest component of BLG granules. Our previous studies suggested that the *Isatis indigotica**root polysaccharide* (*IRPS*) and clemastanin B derived from *IIR* can inhibit various subtypes of the influenza virus *in vitro*. Inhibiting the hemagglutinin (HA) of the virus at its early stage of infection is an important antiviral mechanism of *IIR* [24-26]. *In vivo* experiments revealed clemastanin B to significantly inhibit pneumonia and virus proliferation in lung tissue ([name] and [name], unpublished work). We also found that the lignin group (*IIR* isolated) inhibits the nuclear factor-kappa B signaling activated by the influenza virus and blocks exportation of the NP protein of the influenza virus (article in press). Other studies have also shown that indirubin (also contains *IIR*) and its derivatives have antiviral and anti-inflammatory effects in infection due to the influenza A (H5N1) virus [27].

### Study aims

Studies have suggested that BLG and its active ingredients may inhibit the influenza virus. Little concrete clinical evidence has been provided, however, for the efficacy of BLG in the treatment of seasonal influenza. We wished to evaluate the efficacy and safety of BLG granules for the treatment of seasonal influenza in an evidence-based clinical trial.

## Methods/Design

Ethical approval of the study protocol was granted from the Ethics Committee of the First Affiliated Hospital of Guangzhou Medical University (number, 2011014; Guangzhou, China), and informed consent was obtained from each participant.

### Design

This clinical study was a randomized, double-blind, double control trial that tested drugs and placebo. Noninferiority (versus positive control) and superiority (versus placebo control) trials were conducted. Patients with positive tests for the influenza virus (rapid detection of antigens to the influenza virus before enrollment, but if detection of nucleic acid of the influenza virus or cultivation of the influenza virus was inconsistent, the patient was excluded) were assigned randomly into three groups of equal proportions (1:1:1). Groups were: oseltamivir treatment (positive control), BLG granule treatment (test group) and placebo group. Patients will accept 5-day treatment and 21-day observation. Patient follow-up was undertaken on days 1, 3, 5, 7, 21 (Table 1 and Figure 1). Specific items that were collected for each follow-up period are outlined in Table 1.

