### Number of participants and specimen collection

Recommendations from the World Health Organization for influenza-like illnesses (ILIs) were used as the basis for influenza surveillance. If a patient presents with an acute cough and fever, clinicians must be highly vigilant to test for infections caused by the influenza virus. In general, the rate of ILI cases that lead to a clinical diagnosis of influenza infection is approximately 18 to 80%, which is higher than other clinical diagnoses, for example, acute infections of the upper respiratory tract [28]. We selected adult ILI patients for inclusion into the study. The study was designed to enroll 177 cases.

Specimen collection included pharyngeal/throat swabs and blood samples. Pharyngeal/throat secretions were obtained from the upper respiratory tract of each patient [29]. Pharyngeal/throat swabs will be used to test the mRNA of the influenza virus; the virus will be cultured. Blood samples will be used to test viral antibodies.

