#### Primary outcome

The first primary outcome is the duration of the illness and will be measured in hours. Duration of illness is defined as the time from symptom onset to alleviation of the influenza-like symptoms: nasal obstruction, running nose, cough, sore throat, headache, fatigue, myalgia, chills and sweating. The definition of symptom alleviation is influenza-like symptoms score ≤1 (mild) and maintenance of stable symptoms for more than 24 h [30,32].

Another primary outcome is the time to defervescence, which is measured in hours. The time from the first dose of the study medication to the time when the body temperature decreases to <37.4°C is defined as ‘defervescence,’ and when it is sustained for ≥24 h, it is defined as ‘complete defervescence’ [30,32].

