#### Statistical analyses

The software used for statistical analyses will be SPSS v17.0 (IBM, Armonk, NY, USA) or SAS v9.2 (SAS Institute, Cary, NC, USA).

All statistical inferences will be determined using two-sided tests. *P* <0.05 will be considered significant, and 95% confidence intervals will be used.

Efficacy analyses will use LOCF to compensate for cases not fully covered during treatment. The LOCF approach uses the last data observed, which is transferred to the database to obtain a complete dataset. The safety assessment will not evaluate missing data.

A comparison between the dropout rate and dropout rate caused by adverse events will be undertaken using the Pearson’s χ^2^test.

Data will be described as the mean, standard deviation, and confidence intervals. If necessary, minimum, maximum, P25, P75, and median values will be provided. Paired measurement data will also show the differences between the mean and standard deviation. When using nonparametric methods, median and mean values will be provided. Count data will be described using the frequency distribution and corresponding percentage. Data of concentrations will be described using the frequency distribution and the corresponding percentage, as well as median and average values. Qualitative information will be described using the positive rate, the number of positive cases, and the denominator.

Baseline data analyses (two sets) will include demographic indicators, as well as general, primary and secondary indicators before intervention. Measurement data will be described using a *t*-test or t’ test (if the variance is absent). Count data will be described using the Pearson’s χ^2^test. Rating data will be described using the two-sample Wilcoxon rank sum test.

With respect to analyses of effectiveness, for quantitative variables, comparisons between groups will be undertaken using repeated measures analysis of variance and covariance analysis. For qualitative variables, comparisons between groups will be tested using the Pearson’s χ^2^test, whereas center effect analysis will use CMH. For rating variables, comparisons between groups will be tested using the Kruskal-Wallis test, regression analysis center effect via the CMH test, or grade logistics.

In terms of center effect analyses, the GLM method will be used for quantitative indicators and CMH methods for qualitative indicators. Rating variables will be evaluated and corrected using a logistic regression model.

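### Non-inferiority to oseltamivir is declared, but the stated inference is a set of two-sided difference tests, with confidence intervals tied to no margin and no placebo condition on the claim

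*Protocol article*

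**What the plan says.** Under Design, the Protocol article sets two aims for the three-arm trial: "Noninferiority (versus positive control) and superiority (versus placebo control) trials were conducted". Allocation is 1:1:1, and under Number of participants, "The study was designed to enroll 177 cases". There are two primary outcomes, duration of illness and time to defervescence, both measured in hours.

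The Statistical analyses section then fixes the inference for the whole trial: "All statistical inferences will be determined using two-sided tests". The threshold is P "<0.05 will be considered significant, and 95% confidence intervals will be used". For efficacy it names repeated-measures ANOVA and analysis of covariance for quantitative variables, Pearson's chi-square and CMH for qualitative ones, and Kruskal-Wallis or ordinal logistic methods for ratings. The article gives no margin for either primary outcome, does not say how an interval would decide non-inferiority, and sets no condition involving placebo on the comparison with oseltamivir.

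Two other statements bear on this. The Background section on drug resistance says that "the true effectiveness of oseltamivir treatment against influenza is controversial". The Discussion says a large-scale trial will follow, "based on the results of this pilot study".

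**The concern.** A test of no difference answers a different question from non-inferiority. A significant result can show that BLG is worse or better than oseltamivir. A non-significant one shows only that the data did not separate the two, which is common in a small trial whatever the truth. Non-inferiority needs a limit on acceptable loss and a confidence bound that excludes it. The article declares the aim and describes its inference, and the two do not match.

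There is also the question of assay sensitivity. Being close to oseltamivir means something only if oseltamivir worked in these patients, and the article voices doubt about that. The placebo arm can settle it, but the text does not use that arm to qualify the claim.

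At stake is a report that BLG is as good as oseltamivir when the data cannot bear that statement. It would carry weight, because the Discussion already presents BLG as a much cheaper option.

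**Working it through.** **Inputs from the article.** Total 177, allocation 1:1:1, so 177/3 = 59 per arm; two-sided alpha 0.05. The article gives no margin, effect, SD or power, so 177 itself cannot be reproduced. That is not raised as a point here.

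**Assumptions.** The true oseltamivir effect over placebo is d = 0.2 to 0.5 SD, with d = 0 as the limiting case. The outcome is approximately normal with a common SD, and no patients are lost. An inert BLG has the placebo mean, so the true BLG-oseltamivir difference equals d.

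**Step 1, precision.** SE of a two-arm difference = sqrt(2/59) = 0.184 SD. The 95% half-width is 1.96 × 0.184 = 0.361 SD.

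**Step 2, an inert BLG if non-significance were read as non-inferiority.** P(not significant) = Φ(1.96 − d/SE) − Φ(−1.96 − d/SE). For d = 0.4, d/SE = 2.17, and the result is Φ(−0.21) − Φ(−4.13) = 0.416.

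**Step 3, adding placebo conditions.** The three arms share data, so the joint probabilities come from a simulation of 1,000,000 three-arm trials.

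| d (SD) | BLG vs oseltamivir not significant | and oseltamivir beats placebo | and BLG beats placebo | and both beat placebo |
|---|---|---|---|---|
| 0 | 95% | 2% | 2.06% | 0.47% |
| 0.2 | 81% | 11% | 2.43% | 1.55% |
| 0.3 | 63% | 16% | 2.38% | 1.96% |
| 0.4 | 42% | 16% | 2.13% | 1.99% |
| 0.5 | 22% | 12% | 1.70% | 1.66% |

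Requiring only that oseltamivir beat placebo still lets an inert BLG through 11% to 16% of the time for d = 0.2 to 0.5. Requiring BLG to beat placebo brings this to about 2%.

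**Step 4, check on another scale.** The primary outcomes are durations, so the same question was asked on the hazard-ratio scale. With an event in all 2 × 59 = 118 patients, P(not significant) = Φ(1.96 − ln(HR) × sqrt(118/4)). This gives 83%, 70%, 40% and 18% for HR 1.2, 1.3, 1.5 and 1.7, the same order of size.

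**Step 5, the same trial under a margin rule.** With margin M and true difference δ, P(non-inferiority) = Φ((M − δ)/SE − 1.96).

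- Inert BLG (δ = d): 2.5% if M equals the full oseltamivir effect; 0.05% to 0.6% if M is half of it.
- BLG truly equal to oseltamivir (δ = 0): 19%, 37%, 58% and 78% for M = 0.2, 0.3, 0.4 and 0.5 SD.
- Patients per arm for 80% power, 2 × (1.96 + 0.842)²/M²: 393, 175, 99 and 63.

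**The case against.** The strongest reply is that the method is half there. A two-sided 95% interval is the usual instrument for non-inferiority, and the section plans such intervals. A reader might infer that a difference test at P<0.05 is the only decision rule. The text does not support that: what is missing is the margin and the link from the interval to it. The article is also a condensed account, so a margin may stand in the full protocol, and its absence here is not by itself a fault. What stands is the mismatch within the article: an inferential rule is given for all comparisons, and it does not fit one of the two declared aims.

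A reader might also infer that an inert BLG is likely to be declared non-inferior. The documents do not support this. The article never says that non-significance will count as non-inferiority, and the sentence declaring non-inferiority also declares superiority over a concurrent blinded placebo. An inert BLG would usually fail that second test, and the failure would be visible beside any claim. But the article does not say that both must succeed, so the protection is available and not built in.

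Nor does the Background show that oseltamivir was ineffective in this trial. It reports resistance of at least 90% in 2008-2009, but under 1% in 1999-2007, and gives no oseltamivir resistance figure for the enrolment years from 2012. An oseltamivir-placebo comparison is not excluded either, since the section speaks generally of comparisons between groups.

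Finally, the pilot label lowers the stakes, since a larger trial is meant to follow. It also makes a formal non-inferiority claim harder to justify.

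**Conclusion.** The concern holds in a limited form. The article declares non-inferiority to oseltamivir, yet its stated inference consists of difference tests, its intervals are attached to no threshold, and no success over placebo is required before the claim counts. That analysis cannot yield a non-inferiority conclusion.

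The pass rates of 81% down to 22% for an inert BLG are conditional. They assume oseltamivir effects of 0.2 to 0.5 SD, 59 evaluable patients per arm, and a reading of non-significance that the article does not state. They show what that reading would cost and do not predict what the investigators will do. Adding the declared superiority over placebo as a joint requirement lowers the rate to about 2%.

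**What to change.** Preferred: make superiority of BLG over placebo the inferential claim. Report BLG minus oseltamivir for each primary outcome as an estimate with a 95% confidence interval, and state that a non-significant difference will not be read as non-inferiority. This changes wording only and suits the pilot status. The cost is a more modest statement about oseltamivir.

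If non-inferiority is kept, state a justified margin for each primary outcome, fixed before unblinding. Judge the claim by the 95% confidence limit against that margin in both the modified intent-to-treat and per-protocol sets, and let it count only if oseltamivir and BLG each beat placebo in this trial. If the full protocol already holds such a rule, bring the article's text into line with it. The two-set requirement costs little, since the article already plans to check one set against the other.

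The margin itself is costly. At 59 per arm, power for a truly equal BLG is about 19% to 78% for margins of 0.2 to 0.5 SD, before the placebo conditions reduce it further. Reaching 80% on the margin test alone would take 393 down to 63 per arm. With 50 patients finished by June 2014, the larger figures look out of reach.

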**Table 1 Tab1:** **Follow-up chart of treatment using ban-lan-gen granules against seasonal influenza**

**Visit cycle evaluation projects**	**Screening stage**	**Remedial period**			
	**Visit 0 day 0.5 to 0**	**Visit 1 Day 3 + 1 after administration**	**Visit 2 Day 5 + 1 after administration**	**Visit 3 Day 7 + 1 after administration**	**Visit 4 Day 21 + 7 after administration**
Acquisition of basic medical history					
Informed consent	X				
Basic conditions	X				
Symptoms	X	X	X	X	
Inclusion and exclusion criteria	X				
Safety observations					
Vital signs	X			X	
Electrocardiography	X	a	a	X	
Chest radiograph	X	a	a	a	
Laboratory inspection	X	a	a	X	
Record adverse events	X	X	X	X	X
Efficacy					
Record influenza symptoms	X	X	X	X	
Virology					
Rapid diagnostic tests	X				
Real-time PCR analyses	X	X	X	X	
Viral isolation culture	X	X	X	X	
Viral antibody titer	X				X
Other					
Grouping and giving drugs	X				
Administer drugs	X	X	X		
Distribute patient diary card	X				
Accompanying treatment	A	A	a	a	
Compliance	X	X	X	X	
Inspection results	X				X
Original record completion	X	X	X	X	X
Recover study drug				X	
Recover patient diaries				X	
CRF review, recovering and test summary					X

X, must implement; a, necessary to implement.

**Figure 1 Fig1:**
[figure not shown]
**Study flowchart.** Participants with a rapid diagnosis of influenza will be recruited, and they will be assigned randomly into three different groups. All participants will accept the 5-day treatment and 21-day follow-up period observation. The data were collected to determine the treatment efficacy and safety of Ban-Lan-Gen (BLG)*.*

### Setting

Different aspects of the study activities will be conducted at different sites. For instance, patient enrollment, as well as collection of specimens and data, will be conducted in the Outpatient Department of the First Affiliated Hospital of Guangzhou Medical University. Biochemical examinations will be undertaken in the laboratories of the First Affiliated Hospital of Guangzhou Medical University. Virus testing will be carried out in the Clinical Virology Division of the State Key Laboratory of Respiratory Disease, Guangzhou, China. Data analyses will be done at Southern Medical University, Guangzhou, China.

### Number of participants and specimen collection

Recommendations from the World Health Organization for influenza-like illnesses (ILIs) were used as the basis for influenza surveillance. If a patient presents with an acute cough and fever, clinicians must be highly vigilant to test for infections caused by the influenza virus. In general, the rate of ILI cases that lead to a clinical diagnosis of influenza infection is approximately 18 to 80%, which is higher than other clinical diagnoses, for example, acute infections of the upper respiratory tract [28]. We selected adult ILI patients for inclusion into the study. The study was designed to enroll 177 cases.

Specimen collection included pharyngeal/throat swabs and blood samples. Pharyngeal/throat secretions were obtained from the upper respiratory tract of each patient [29]. Pharyngeal/throat swabs will be used to test the mRNA of the influenza virus; the virus will be cultured. Blood samples will be used to test viral antibodies.

